#### Data Analysis

Data analysis will be performed using the Epi Info (Centers for Disease Control and Prevention) software. The primary analysis will be conducted under the intention-to-treat principle. For individual outcomes, proportions will be compared using the chi-square test, and continuous measures will be compared using 2-tailed *t* tests. Stratified analysis will be conducted to control for confounding and assess the effect modification by demographic variables and medication adherence. The effects of the intervention will be tested by ANOVA, which will allow adjustment for baseline differences between groups. Two-sided *P* values and 95% CIs will be used to determine statistical significance of results.

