### Study Setting

The study will be conducted in 14 primary health care clinics in the city of Harare; these clinics were purposefully selected from a total of 39 health facilities (12 polyclinics, 6 family health services clinics, 15 satellite clinics, and 2 infectious diseases hospitals) in the city. The 14 facilities that have been selected for the study are the ones that offer comprehensive services, including curative services, chronic pain care, maternal and child health services, HIV prevention services, and community health services. These clinics are in the high-density suburbs of the city, with each clinic serving a population of 80,000-100,000 people, the majority of whom are socioeconomically disadvantaged. The 14 health facilities will be randomly allocated into either the intervention or the control arm. Thus, each study arm will comprise 7 health facilities.

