#### Randomization

All 14 targeted health facilities will be randomly allocated to either the intervention or the control arm. Each arm will consist of 7 clinics. The randomization process will be conducted by an official from the city of Harare, from the City Health Department, who will not be part of the study staff. The randomization process will be done using the simple randomization technique, based on computer-generated random numbers. To reduce bias and improve study fidelity, group allocation will be concealed to the data collectors until the completion of baseline data collection.

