##### Sample Size

Based on the recommendations for sample size calculation for cluster randomized controlled trials with a fixed number of clusters [32], a total of 680 participants will be required for the trial. Therefore, the study will comprise 14 clusters, with 49 participants per cluster. The sample size was calculated using the following parameters, obtained from the review of literature: 80% study power, 0.5 effect size, 1 SD, 0.05 coefficient of variation, and 20% lost to follow-up adjustment.

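### Clinics are randomised, but the planned chi-square, t and ANOVA tests take no account of clinic, so P values come out too small and confidence intervals too narrow

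*Protocol article*

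**What the plan says.** The unit of randomisation is clear. Study Setting says: "The 14 health facilities will be randomly allocated into either the intervention or the control arm". The Randomization section repeats it and adds: "Each arm will consist of 7 clinics". The Sample Size section also works at cluster level, opening with "Based on the recommendations for sample size calculation for cluster randomized controlled trials with a fixed number of clusters" and concluding that "the study will comprise 14 clusters, with 49 participants per cluster".

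The Data Analysis section changes level. It says "For individual outcomes, proportions will be compared using the chi-square test, and continuous measures will be compared using 2-tailed" t tests, and then "The effects of the intervention will be tested by ANOVA", with adjustment for baseline differences between the groups. Two-sided P values and 95% confidence intervals from these tests are to determine statistical significance. Clinic does not appear in that section, and nowhere does the article mention an ICC, a random clinic effect, generalised estimating equations, a cluster-robust variance or a clinic-level summary.

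**The concern.** Patients of one clinic live in the same catchment area and share clinic staff and usual care. In the intervention arm they also receive sessions and visits from community health workers. Their blood pressure, HbA1c and reported behaviour are therefore likely to be more alike than those of patients from different clinics. A test that treats them as independent ignores the between-clinic variance and understates the standard error of the treatment difference.

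It also overstates how much information there is about the error. With 39 analysed per clinic, a patient-level t test refers to 14 × 39 − 2 = 544 degrees of freedom, whereas the randomisation supplies 14 − 2 = 12.

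The bias runs towards false positives and affects the primary outcomes. The article's Strengths and Limitations section says a successful intervention could be scaled up nationally, so a spurious positive result would have consequences.

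**Working it through.** **Inputs from the protocol.** 7 clinics per arm (Randomization); 49 enrolled per clinic and 20% loss to follow-up (Sample Size); two-sided tests with 95% intervals, hence a 5% level (Data Analysis). Patients analysed per clinic: m = 49 × 0.80 = 39.2, taken as 39.

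**Input not in the protocol.** The ICC. The Sample Size section gives a coefficient of variation of 0.05 without saying what it refers to. A range of ICCs from 0.01 to 0.10 is assumed below.

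**Can the plan's own figure supply the ICC?** Not reliably. An effect of 0.5 SD, 80% power and a two-sided 5% level need n = 63 per arm without clustering. With k = 7 clinics per arm, the fixed-cluster formula is m = n(1 − ICC)/(k − n × ICC).

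- Reading 0.05 as the ICC: 63 × 0.95/(7 − 3.15) = 15.5, so 16 per clinic, 224 in total, and 224/0.80 = 280 after loss. The plan states 680.
- Reaching the plan's size requires an ICC of about 0.088: 39 per clinic, 546 in total, and 546/0.80 = 682.5.
- Reading 0.05 as a between-clinic coefficient of variation of a proportion of 0.5 gives an ICC of 0.05² × 0.5/(1 − 0.5) = 0.0025. For a mean, the result depends on an outcome mean that is not given.

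The stated inputs therefore do not fix the ICC. That 680 cannot be reproduced is a separate matter.

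**Type I error of the patient-level test.** Design effect: DE = 1 + (m − 1) × ICC = 1 + 38 × ICC. The patient-level standard error is too small by a factor of about √DE, so the true two-sided error is about 2 × [1 − Φ(1.96/√DE)].

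| ICC | DE | √DE | True error of nominal 5% test |
|---|---|---|---|
| 0.0025 | 1.095 | 1.05 | 6.1% |
| 0.01 | 1.38 | 1.17 | 9.5% |
| 0.02 | 1.76 | 1.33 | 14.0% |
| 0.03 | 2.14 | 1.46 | 18.0% |
| 0.05 | 2.90 | 1.70 | 25.0% |
| 0.088 | 4.33 | 2.08 | 35% |
| 0.10 | 4.80 | 2.19 | 37% |

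Worked line for ICC 0.05: 1.96/1.703 = 1.151, and 2 × [1 − Φ(1.151)] = 0.25.

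**Check by simulation** (20,000 null trials per setting, 7 against 7 clinics, 39 per clinic). At ICC 0.05 the patient-level t test rejected in 25.3% of trials and the chi-square test in 26.0%, and nominal 95% intervals covered 74.7%. At ICC 0.01 the t test rejected in 9.4%, and at 0.10 in 37% to 38%. With no loss to follow-up (49 per clinic) and ICC 0.05, DE is 3.4 and the simulated error is 29.2%.

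**The same simulations with a valid test.** A t test on the 14 clinic means (12 degrees of freedom) rejected in 4.7% to 5.3% of null trials at every ICC from 0 to 0.10. Its power for a 0.5 SD effect with 39 per clinic is 98% at ICC 0.02, 88% at 0.05 and 69% at 0.10.

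**The case against.** Four points can be made for the plan.

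1. **The article does not state the unit of analysis.** A t test on clinic means is valid, as is ANOVA with clinic as a random or nested factor. This is true, but the text says neither. It applies chi-square and t tests to individual outcomes and describes the ANOVA's adjustment only in terms of baseline. Patient level is the natural reading.

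2. **Detail may sit in an analysis plan that is not shown, and Study Design commits the trial to the CONSORT statement for cluster trials.** The degrees-of-freedom method or the variance correction could properly be left to such a plan. Here, however, the article names the tests that decide significance, and they do not match the design. The CONSORT commitment names no analysis method and does not alter that.

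3. **The true ICC may be small.** This stands as a limit on the size of the problem. Under one reading of the 0.05 coefficient of variation the ICC is 0.0025 and the error only about 6%. The document does not establish that reading, and an ICC of about 0.088 would fit the stated sample size better.

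4. **Baseline adjustment may reduce the between-clinic variance.** It may, and the simulations above do not include it. It does not remove clustering, and it leaves the degrees of freedom wrong.

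**Conclusion.** The concern holds. The trial is designed and sized as a cluster trial, but the analysis it states takes no account of clinic. For any positive ICC the P values are too small and the intervals too narrow.

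The size depends on an ICC that the protocol does not give. With 39 analysed per clinic the true error is about 9.5% to 25% for an ICC of 0.01 to 0.05. The 25% is an illustration at 0.05 and not a ceiling: it is 37% at 0.10, and about 6% if the ICC is as low as 0.0025. These figures assume equal clinic sizes and no baseline adjustment. The direction of the error does not depend on those assumptions. This must be corrected before the outcomes are compared.

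**What to change.** Replace the test specification in Data Analysis with one that respects the unit of randomisation and covers every comparison between arms, including the stratified analyses:

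- **Continuous outcomes:** either a mixed model with a random clinic intercept, baseline value as covariate and Kenward-Roger or Satterthwaite degrees of freedom, or a t test on the 14 clinic summaries with 12 degrees of freedom.
- **Binary outcomes:** either a t test on clinic-level proportions, or GEE with a small-sample variance correction suited to 14 clusters.
- **Reporting:** the estimated ICC for each primary outcome.

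Choose one method per outcome and record the choice before outcome data are compared by arm.

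**Cost.** No new data and no change to conduct. The clinic-summary option needs only a t test, which the plan already intends to run; a mixed model or GEE needs software that can fit it. Intervals will be wider. At an ICC of 0.05 the factor is 1.70 from the design effect, times 2.18/1.96 = 1.11 for 12 degrees of freedom, or about 1.9 in all. Power for a 0.5 SD effect stays above 80% at that ICC (88%), but falls to 69% if the ICC is 0.10.

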#### Outcome Measures

The outcome evaluation for this study will be based on data collected both at baseline and during the postintervention follow-up (after 6 months). Data collection tools will be identical for data collection at both periods and include information on patient’s demographics, disease history, lifestyle behaviors, medication use, primary use of health care services, and hospitalizations. Height, weight, waist circumference, glycosylated blood glucose levels, and blood pressure will also be measured.

The primary study outcomes will be blood pressure and blood glucose levels as well as levels of adherence to recommended lifestyle modifications. Other outcomes will include changes in medication adherence and additional health-related outcomes, such as frequency of hospitalization or the occurrence of complications.

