##### Hypertension and Diabetes Control

Patient’s hypertension and diabetes control will be assessed by blood pressure and HbA_1c_ measurements, respectively*.* Blood pressure of 140/90 mm Hg or higher will be considered uncontrolled hypertension, while an HbA_1c_ level above 8% (53 mmol/mol) will be considered uncontrolled diabetes [27].

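### The Data Analysis section lists an unadjusted test and a baseline-adjusted ANOVA for the same outcomes and does not say which one decides

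*Protocol article*

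**What the plan says.** **Which outcomes are primary.** Outcome Measures states: "The primary study outcomes will be blood pressure and blood glucose levels as well as levels of adherence to recommended lifestyle modifications". The abstract likewise speaks of levels for blood pressure and glucose.

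**How two of them are also classified.** The subsection Hypertension and Diabetes Control falls under the heading on assessing primary and secondary outcomes. It gives cut-offs for the same measurements. For the first: "Blood pressure of 140/90 mm Hg or higher will be considered uncontrolled hypertension". It sets a similar cut-off for HbA1c. It does not say whether this classification is primary or secondary.

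**How they are tested.** Data Analysis gives three routes in one paragraph:
- An unadjusted comparison, by chi-square for proportions and by t test for continuous measures.
- A stratified analysis, aimed both at confounders and at differences in effect between subgroups.
- A baseline-adjusted test: "The effects of the intervention will be tested by ANOVA, which will allow adjustment for baseline differences between groups".

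The paragraph closes with a single rule: significance is read from two-sided P values and 95% intervals. It does not say from which of these analyses. The only thing fixed about the primary analysis is that it follows intention to treat.

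**The concern.** Followed as written, the paragraph produces at least two P values for the arm difference in blood pressure: one from a t test that ignores baseline and one from a test that adjusts for it. The two use the same data but are different tests, and one can be significant when the other is not. If control status is also compared as a proportion, there is a third.

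With no ranking, whichever result is significant can be reported as the effect on that outcome. Two things are at stake. The chance of a false claim for one outcome rises above the nominal 5%. And when the true effect is modest, the trial's answer may depend on which test is reported. Reducing the primary outcomes to one would not cure this, because the chosen outcome would still have rival tests.

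**Working it through.** **Inputs from the article.** Sample Size gives 680 participants, 20% loss, a planned effect of 0.5 and SD 1. Analysed: 680 × 0.8 = 544, or 272 per arm. The 5% level is implied by the 95% intervals. The article states no error rate for this issue, so there is no figure to reproduce. How 680 was derived is a separate question, and nothing here depends on it.

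**Assumptions not in the article.** Normal outcome; correlation r between baseline and 6-month value of 0.3, 0.5 or 0.7; adjustment done by analysis of covariance, which is what the ANOVA sentence seems to intend; control status cut at the median or nearby; patients treated as independent, to isolate this point from clustering.

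**Step 1: the two tests of the level.** For a true difference of d SD:
- t test: standard error √(2/272) = 0.0857, so z = d/0.0857.
- Adjusted test: standard error 0.0857 × √(1 − r²).
- Correlation between the two test statistics: √(1 − r²) = 0.954, 0.866, 0.714 for r = 0.3, 0.5, 0.7.

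**Step 2: no true effect.** The chance that at least one test is significant is 1 − P(|Z₁| < 1.96 and |Z₂| < 1.96), with that correlation. Two independent tests would give 1 − 0.95² = 9.75%, and three 1 − 0.95³ = 14.3%; these are upper bounds.

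| Tests that may decide | r = 0.3 | r = 0.5 | r = 0.7 |
|---|---|---|---|
| t or adjusted, formula | 6.4% | 7.3% | 8.3% |
| t or adjusted, simulated | 6.4% | 7.5% | 8.6% |
| plus chi-square on control status, simulated | 9.1% | 10.2% | 11.1% |

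A second simulation gave 6.0% to 8.9% for two tests and 8.8% to 11.8% for three.

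**Step 3: a true effect.** At d = 0.2 the t test has z = 0.2/0.0857 = 2.33, so power is Φ(2.33 − 1.96), about 65%. At r = 0.5 the adjusted test has z = 2.33/0.866 = 2.69 and power of about 77%. Simulated power for chi-square on control status is about 45%.

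Share of trials in which the tests disagree on significance (ranges over r = 0.3 to 0.7 and over the cut for control status):

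| True effect | t vs adjusted | all three |
|---|---|---|
| 0.2 SD | 9% to 31% | 31% to 52% |
| 0.3 SD | 3% to 7% | 19% to 29% |
| 0.5 SD (planned) | below 1% | 0.1% to 1.6% |

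For the middle column the formula gives 9%, 17% and 28% at 0.2 SD for r = 0.3, 0.5 and 0.7, in line with the simulated 9%, 18% and 31%. At 0.5 SD the t test has z = 5.83 and power near 100%, so there is almost nothing left to disagree about.

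**Step 4: the lifestyle outcomes.** Table 2 classifies patients on each recommendation as adherent or nonadherent. The unadjusted test for these is chi-square. ANOVA of a yes/no result is not a fitting adjusted analysis, so the second test is poorly specified for these primary outcomes. The level-versus-control issue does not arise for them.

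**The case against.** The strongest reply is that the paragraph does give the effect-testing role to one method. Only the ANOVA is said to test the effects of the intervention; the t and chi-square sentence speaks of comparing outcomes. On that reading the simple comparisons are descriptive. This is natural and may be what was meant. But the article does not say so, and it applies one significance rule to every result. What stands of the objection is that one sentence would settle the matter.

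Second, a reader might infer that blood pressure and HbA1c each have three deciding tests, with the false-positive rate roughly doubled. The article does not support that. Both the abstract and Outcome Measures make levels primary, and nowhere is control status called a primary outcome. The 9% to 12% figure is therefore conditional; without control status it is 6% to 9%.

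Third, a reader might infer that the tests often disagree and that the weaker ones lose much power. That holds at 0.2 SD, a value not in the article, and not at the planned 0.5 SD.

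Fourth, ranking analyses is commonly left to an analysis plan, which is not shown here. A bare omission would be no finding. Here, however, the article itself states competing tests under one rule. If an analysis plan ranks them, the article's wording still needs to match it.

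**Conclusion.** The point holds in limited form. The article sets an unadjusted and a baseline-adjusted test side by side for the same outcomes and does not say which decides. For blood pressure and HbA1c it also leaves the standing of control status open.

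The inflation within one outcome is moderate, because the tests are strongly correlated, and it arises only if any of them may decide. Disagreement matters for true effects well below the planned 0.5 SD. Such effects are possible, but the article does not plan for them.

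All figures rest on 272 per arm, a normal outcome, baseline correlations of 0.3 to 0.7 and no clustering. The last assumption matters most. At an assumed intraclass correlation of 0.05, the t test alone has a simulated false-positive rate of about 24%, which dwarfs the effect described here. Accounting for clinics is a separate and larger problem, and this point is secondary to it. It is still worth correcting because the correction costs little.

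**What to change.** Change the wording of Data Analysis in three places:
- **Blood pressure and HbA1c.** State that the deciding analysis is the between-arm difference in the 6-month level, from one model adjusted for the baseline value (analysis of covariance or a mixed model) that respects the clinic as the randomised unit.
- **Other comparisons.** State that control status and the unadjusted t and chi-square comparisons are supportive and carry no claim of effectiveness on their own.
- **Lifestyle classifications.** Name one baseline-adjusted analysis suited to binary outcomes, also respecting the clinic, in place of ANOVA.

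No new data are needed, since Outcome Measures already provides for baseline and 6-month collection with identical tools. The wording should be fixed before outcomes are compared between arms, and the team should confirm that its software can fit the chosen models. The cost is that a significant unadjusted or control-status result can no longer be presented as the primary finding.

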We have developed a simple CHW health literacy intervention on lifestyle modification, and we have designed a study to evaluate the effects of the intervention among patients with hypertension and diabetes in the city of Harare, Zimbabwe. This paper describes our research design and discusses the rationale of our study. We hypothesize that the intervention will have a positive effect on (1) adherence to recommended lifestyle modifications, (2) adherence to medication, as well as (3) blood glucose and blood pressure levels.

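### ANOVA as named does not give the baseline adjustment claimed for it, and stratification by medication adherence, itself an outcome, is not restricted to the baseline measurement

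*Protocol article*

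**What the plan says.** The Data Analysis section of the protocol article lists chi-square tests for proportions and two-tailed t tests for continuous measures. It then says: "The effects of the intervention will be tested by ANOVA, which will allow adjustment for baseline differences between groups". It gives no covariate, no regression model and no repeated-measures structure.

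The same section says: "Stratified analysis will be conducted to control for confounding and assess the effect modification by demographic variables and medication adherence". It does not say at which visit adherence is taken for this purpose.

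Medication adherence has another role elsewhere. The Introduction says: "We hypothesize that the intervention will have a positive effect on (1) adherence to recommended lifestyle modifications, (2) adherence to medication". Outcome Measures says: "Other outcomes will include changes in medication adherence and additional health-related outcomes". Outcome Measures sets outcome evaluation at baseline and at 6 months and adds: "Data collection tools will be identical for data collection at both periods". The section on assessing outcomes places medication adherence in section E of the questionnaire, so an MMAS-8 score will exist at both visits.

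The Randomization section allocates 14 clinics, 7 per arm, by simple randomisation and mentions no stratification or matching.

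**The concern.** There are two problems with how the adjustment is set out.

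First, the protocol credits ANOVA with a property that it lacks unless a baseline covariate is added. The possible readings of the word give different answers when the arms differ at baseline, and two of them err in opposite directions. With few clinics and unrestricted allocation, baseline differences are a realistic prospect, and the analysis is the only stated protection against them.

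Second, medication adherence is named as a stratifier although the trial expects the intervention to change it. If the strata were formed from follow-up adherence, the comparison within strata would remove part of any effect on blood pressure and HbA1c that runs through adherence. It would also compare groups that differ in unmeasured respects. The text does not exclude this.

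**Working it through.** The plan gives no figure on this point to reproduce. The inputs from the documents are 7 clinics per arm and 49 participants per clinic (Sample Size, Study Setting), and a target effect of 0.5 with SD 1 and 20% loss to follow-up (Sample Size). That section gives a coefficient of variation of 0.05 but no ICC. Two readings are therefore carried as assumptions: ICC 0.05, and ICC 0.0025 (0.05 squared, taking the 0.05 as the coefficient of variation of clinic means with SD equal to the mean).

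**Step 1. Does ANOVA add anything to the t test?** With two arms, F = t². In a check with 272 per arm (680 × 0.8 / 2), F and t² were both 5.767 and p was 0.0167 for both. One-way ANOVA therefore adds no baseline adjustment.

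**Step 2. How large can a chance baseline difference be?** SD of the difference between arms = √(2 × DE / (7 × 49)), with DE = 1 + 48 × ICC.

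- ICC 0.0025: DE = 1.12; √(2.24/343) = 0.081; × 1.96 = 0.16 SD.
- ICC 0.05: DE = 3.4; √(6.8/343) = 0.141; × 1.96 = 0.28 SD.

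These are the differences exceeded, in either direction, in 5% of allocations.

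**Step 3. How much reaches the result?** Let d be the baseline difference and r the baseline to follow-up correlation, with equal SDs at the two visits and the same r between clinic means as between individuals. With no true effect, a follow-up comparison estimates r × d, a change-score comparison (r − 1) × d, and ANCOVA 0. For d = 0.276:

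- r = 0.5: 0.5 × 0.276 = 0.14 SD unadjusted.
- r = 0.7: 0.7 × 0.276 = 0.19 SD unadjusted.

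The target is 0.5 SD, so these are about 28% and 39% of it.

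A simulation with 272 per arm, true effect 0, imbalance 0.3 SD and no clustering confirms the pattern:

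| r | ANOVA on follow-up | Change or group-by-time ANOVA | ANCOVA |
|---|---|---|---|
| 0.3 | +0.09 | −0.21 | about 0 |
| 0.5 | +0.15 | −0.16 | about 0 |
| 0.7 | +0.21 | −0.09 | about 0 |

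**Step 4. What precision is gained?** Adjustment cuts individual-level residual variance by r², that is 25% at r = 0.5 and 49% at r = 0.7. At ICC 0.05 the individual-level part is 0.95 of a design effect of 3.4. If baseline explains nothing between clinics, the variance of the arm difference falls by 0.95 × 0.25 / 3.4 = 7% or 0.95 × 0.49 / 3.4 = 14%. The gain is larger if clinic means also correlate over time, as Step 3 assumes.

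**Step 5. Does the time point of adherence matter?** In an assumed model, an unmeasured trait drives both adherence and the outcome, and the intervention raises latent adherence by 0.3, 0.5 or 0.8. Lower outcome values are better; there is no clustering.

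| Shift in adherence | Total effect | Baseline strata | Follow-up strata | Follow-up strata, no true effect on outcome |
|---|---|---|---|---|
| 0.3 | −0.23 | −0.23 | −0.15 | +0.05 |
| 0.5 | −0.25 | −0.25 | −0.12 | +0.07 |
| 0.8 | −0.29 | −0.29 | −0.08 | +0.12 |

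Baseline strata recover the total effect and give about 0 when there is none. Follow-up strata do neither. The sizes depend on the assumed model; the direction of the problem is what matters here.

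**The case against.** The sentence plainly intends baseline adjustment, and ANOVA may be loose wording for ANCOVA or for a repeated-measures analysis of the two visits. Outcome Measures speaks of changes in medication adherence, so a t test on changes, which also uses baseline, cannot be excluded. This stands. A reader might infer that the planned adjustment cannot work under any reading, and the document does not support that. But the readings disagree (Step 3), and only the covariate model delivers the stated property.

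On adherence, the phrase naming demographic variables and medication adherence may attach to effect modification alone, so that adherence is never called a confounder. Baseline adherence is collected and is a legitimate stratifier. This also stands. A reader might infer that the trial will condition on an outcome; the text only leaves that open. Subgrouping by follow-up adherence would be unsound under either parsing, so the time point needs stating.

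On size, randomisation keeps the unadjusted follow-up comparison unbiased on average, so the baseline half concerns precision and the error in a particular allocation. It would be wrong to read the 0.28 SD as passing whole into the result, since it is multiplied by the correlation. It would also be wrong to read the 25% and 49% as the precision gained for the arm effect. Finally, hospitalisation and complications come from clinic records, so not every outcome has a baseline value from the same tool.

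**Conclusion.** The point holds in a limited form: a method is credited with a property it lacks as named, and a stratifier expected to respond to the intervention has no time point fixed. This is not proof that the eventual analysis will be biased.

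The chance baseline difference exceeds about 0.16 to 0.28 SD in 5% of allocations (assumed ICC 0.0025 to 0.05). From the upper value, about 0.14 to 0.19 SD would enter an unadjusted follow-up comparison at an assumed r of 0.5 to 0.7. The change-score reading errs the other way. The adherence bias arises only if follow-up adherence defines the strata. The ICC, the correlations and the adherence model are all assumptions, because the protocol gives none of them. The change is worth making because it affects the effect estimate and the needed baseline values are already collected.

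**What to change.** Replace ANOVA by ANCOVA for outcomes measured at both visits: regress the 6-month value on arm and the baseline value of the same outcome, and use logistic regression with baseline status for binary outcomes. Fit it in a model that accounts for clinic with a method suited to 14 clusters. The section names Epi Info, so confirm that it can fit such a model or name software that can.

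State that stratification by medication adherence uses only the baseline MMAS-8 category, that effect modification is tested by an arm-by-baseline-adherence interaction, and that follow-up adherence is not used to control confounding.

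The cost is a change of wording and slightly more analysis work, with no new data. The precision gain should not be oversold: about 7% to 14% of the variance of the arm effect at ICC 0.05 and r of 0.5 to 0.7, more if clinic-level baseline and follow-up values are strongly correlated.
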